## Abstract

Procrastination is more than just a common human foible; it is a ubiquitous behavioral disorder that can negatively impact learning, productivity, and mental health. The psychological and neurological mechanisms underlying chronic procrastination are surprisingly complex, involving impairments in self-control, emotional regulation, and episode anticipation networks, and may lead to emotional distress, reduced self-confidence, and even physical symptoms that in turn can exacerbate procrastination. The aim of this proposed study is to investigate the clinical efficacy of acupuncture for university students with severe procrastination tendencies, to compare the efficacy of acupuncture to other potential interventions (Tai Chi and running exercise), and to examine the effects of acupuncture on cognitive functions related to procrastination. This parallel randomized controlled clinical trial will be conducted at the Third Affiliated Hospital of Henan University of Chinese Medicine, Henan Province, China. A total of ninety full-time college students will be randomly divided into three equal groups (acupuncture group, running group, and Tai Chi group). Each group will receive the assigned intervention for 30 min per session, 3 times per week on alternating weekdays, for a total of 4 weeks. The General Procrastination Scale (GPS) will serve as the primary outcome measure, while the Procrastination Assessment Scale for Students (PASS) and Physical Activity Rating Scale 3 (PARS-3) will be used as secondary outcome measures. Assessments using these outcome measures will be conducted at baseline (0 week) as well as after 2 and 4 weeks of intervention. Scalp electroencephalography (EEG) will be used to measure event-related potentials P300 and N200 during the Go/No-go Emotion Detection task and Task Initiation Delay Paradigm (TIDP) to investigate the impacts of these interventions on cognitive control and error detection abilities.

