#### Inclusion criteria

Preset study inclusion criteria are as follows:

Full-time university student;GPS score ≥ 70 points;No psychotropic drug intake or related acupuncture treatment within the past 30 days;Providing informed consent.

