### Data analysis

The primary analysis will be conducted using a linear mixed-effects model, with fixed effects for group (acupuncture, running, Tai Chi), time (baseline, week 2, week 4), and their interaction, and a random intercept for participants to account for within-subject correlation due to repeated measurements. Baseline GPS score, age, sex, and baseline ERP indices will be included as covariates to control for inter-individual variability in procrastination-related traits.

This mixed-effects modeling framework constitutes the primary analytic strategy and will be implemented under the intention-to-treat (ITT) principle, allowing inclusion of all available observations without imputing missing values, under a missing-at-random assumption.

Prior to model fitting, distributional characteristics of continuous variables will be assessed using the Shapiro–Wilk test. Descriptive comparisons of baseline demographic and clinical characteristics will be performed using analysis of variance (ANOVA) or the Kruskal–Wallis test for continuous variables, and chi-square or Fisher's exact tests for categorical variables, as appropriate, to ensure baseline comparability between groups.

Secondary and exploratory analyses may include pairwise comparisons or non-parametric tests (e.g., Mann–Whitney *U*-test or Wilcoxon signed-rank test) where appropriate for specific outcomes or sensitivity checks. For outcomes with repeated measurements that meet parametric assumptions, repeated-measures ANOVA may be used as a supplementary analysis; otherwise, non-parametric alternatives such as the Friedman test will be applied.

Sensitivity analyses will be conducted to evaluate the robustness of the primary findings, including per-protocol analyses restricted to participants with adherence ≥80% and models incorporating adherence (number of completed sessions) as a continuous covariate.

For secondary outcomes and exploratory ERP analyses involving multiple indices or task conditions, false discovery rate (FDR) correction will be applied within pre-defined families of related comparisons. Statistical significance will be defined as a two-sided *P*-value < 0.05. All analyses will be performed using PASS 18.0, with statistical consultation provided by an institutional biostatistician.

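### The Friedman test, the only named fallback for the supplementary repeated-measures ANOVA, has no group term and so cannot compare the three arms

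*Protocol article*

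**What the plan says.** The Abstract gives the comparison of arms as an aim: "to compare the efficacy of acupuncture to other potential interventions (Tai Chi and running exercise"). PASS and PARS-3, the secondary outcomes, are scheduled with the GPS at baseline, week 2 and week 4 in three parallel arms of 30.

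The Data analysis section fixes the primary method first: "The primary analysis will be conducted using a linear mixed-effects model, with fixed effects for group (acupuncture, running, Tai Chi"), together with time and the group-by-time interaction. A later paragraph turns to other analyses. It opens with "Secondary and exploratory analyses may include pairwise comparisons or non-parametric tests", and gives Mann–Whitney and Wilcoxon signed-rank as examples. It then splits repeated outcomes by distribution. The parametric branch begins "For outcomes with repeated measurements that meet parametric assumptions", and the sentence ends: "repeated-measures ANOVA may be used as a supplementary analysis; otherwise, non-parametric alternatives such as the Friedman test will be applied".

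The parametric branch is thus optional, the non-parametric branch is worded as definite, and Friedman is the only method named in it. Kruskal–Wallis appears in the section only for baseline comparisons.

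**The concern.** In a three-arm parallel trial, the useful term of a repeated-measures ANOVA is group by time: do the arms follow different courses? The Friedman test is the rank counterpart of a one-sample repeated-measures analysis with time as its only factor. The two branches of the sentence therefore answer different questions, and the data decide which question is asked.

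On the Friedman branch, any improvement shared by all arms (practice, expectation, passage of time) counts towards significance although it says nothing about acupuncture against exercise. A real difference between arms is invisible unless it also moves the average over all participants. Running the test arm by arm does not help: significance in one arm and not in another is not a test of the difference between them.

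**Working it through.** **What the statistic contains.** The plan attaches no figure to this branch, so there is none to reproduce. With N participants, k = 3 visits and R_j the sum of within-participant ranks at visit j,

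Q = [12 / (N·k·(k+1))] · ΣR_j² − 3N(k+1) = (1/N)·ΣR_j² − 12N,

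referred to chi-square on 2 degrees of freedom. Arm does not appear. Relabelling every participant's arm leaves Q unchanged.

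Two extremes with N = 81 (3 arms of 27, the protocol's number per arm before the 10% dropout allowance; 27/0.90 = 30):

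- Every participant falls at each visit, in all arms alike. Rank sums are 243, 162 and 81. Q = (59,049 + 26,244 + 6,561)/81 − 972 = 1,134 − 972 = 162, the largest possible value, with no difference between arms.
- One arm falls, one is flat and one rises by the mirror image. Expected rank sums are 162 at each visit. Q at those sums = 3·26,244/81 − 972 = 972 − 972 = 0, with a large difference between arms.

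**Simulation.** Inputs from the protocol article: 27 per arm; three visits; SD 6.8 (pilot acupuncture arm, Sample size); correlation 0.756 between visits (4-week test–retest of the GPS, Primary outcome); alpha 0.05. Assumed: normal data, the mean changes below, and half of each change reached by week 2. There were 4,000 runs. The between-arm test is Kruskal–Wallis on change from baseline to week 4.

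| Change by week 4, three arms | Pooled Friedman rejects | Between-arm test rejects |
|---|---|---|
| 0, 0, 0 | 5.0% | 5.0% |
| −5, −5, −5 (arms identical) | 100% | 5.1% |
| −5, 0, +5 (no average change) | 2.8% | 100% |
| −8, −5, −2 | 100% | 98.2% |

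In the last row Friedman rejects, but it does so equally in the second row, where the arms are the same. Its result does not separate the two cases.

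Run separately in each arm with no change anywhere, at least one arm is significant in 14.4% of runs. The expected value for three independent tests is 1 − 0.95³ = 14.3%.

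**Smaller shifts.** Five points is large: 5/6.8 = 0.74 SD of the score. A second simulation used 30 identical arms' members per group, a skewed outcome and common week-4 shifts of 0.2, 0.3 and 0.5 SD. Pooled Friedman rejected in 35%, 66% and 98% of runs at a visit correlation of 0.6, and in 51%, 86% and 99.9% at 0.75. A repeat with normal data, with half the shift at week 2, agreed within 2 percentage points, and Kruskal–Wallis on change stayed at 4–6%.

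**Missing visits.** Friedman also needs all three visits from each participant, whereas the plan's stated approach for the mixed model is to use all available observations.

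**The case against.** Four points can be made for the plan.

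1. *The primary result is safe.* This stands. The mixed model is fixed as the primary strategy, and no sentence switches GPS from it to Friedman. A reader might infer that any non-normal outcome loses its arm comparison. The document does not support that: the fallback belongs to supplementary, secondary and exploratory work on repeated outcomes.

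2. *Other methods remain open.* This stands in part. Friedman is given as an example, and Mann–Whitney, which does compare arms, is listed in the same paragraph. But Mann–Whitney is optional and pairwise, and the one method named for this branch cannot compare arms. That is a stated method that does not match its parametric partner, not a detail left to an analysis plan.

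3. *Change within an arm is of interest too.* This also stands in part. The Expected results section frames several ERP hypotheses as change after intervention, and Friedman can describe that. The plan nowhere says that a significant Friedman result will be read as a difference between arms. But it does not limit the test to within-arm description either, and it offers it in place of an analysis that can carry group by time.

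4. *The trigger is not spelled out.* This stands. It is tempting to argue that, because entry requires "GPS score ≥ 70 points", baseline GPS is truncated, fails Shapiro–Wilk by design, and so drives the switch. The plan says "Prior to model fitting, distributional characteristics of continuous variables will be assessed using the Shapiro–Wilk test", but it does not tie that check to the Friedman branch. The cut-off truncates baseline GPS only, not later GPS, PASS or ERP values, and how often the check would fail depends on a source distribution that the article does not give. That argument should not be made.

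**Conclusion.** The point holds for secondary, exploratory or supplementary repeated outcomes that reach the Friedman branch, such as PASS, PARS-3, or ERP indices if they are measured repeatedly. For these, the named test cannot show whether acupuncture, running and Tai Chi differ. This follows from the definition of the test and needs no assumption.

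The size of the error depends on how far all arms move together, which the documents do not fix. Under the assumptions above, the false signal with identical arms runs from 35% at a common shift of 0.2 SD (correlation 0.6) to 100% at 5 points. The case in which a true difference is missed (2.8% rejection) needs arms that move in opposite directions. Since the protocol expects improvement after every intervention, the false signal is the more realistic harm.

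The primary GPS comparison, the sample size and the conduct of the trial are unaffected. This is a correction that should be made, not a threat to the main result.

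**What to change.** Replace the second half of the sentence. For secondary and exploratory repeated outcomes, use one of these:

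- the mixed model with group, time and group by time, with robust standard errors or bootstrap intervals where residuals are clearly non-normal; this also keeps participants with a missed visit; or
- a named rank method with a group factor: rank ANCOVA (Quade) of the week-4 value on baseline across the three arms, or Kruskal–Wallis on change from baseline, with the matching pairwise tests of acupuncture against running and against Tai Chi.

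State that assumptions are judged on model residuals. Keep Friedman, if at all, as a description of change within an arm, and say that it will not be used to compare arms.

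The cost is a few lines in the Data analysis section. No new data and no further participants are needed.

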### Ethics and dissemination

This study involves human participants. All research protocols have been reviewed and approved by the Institutional Ethics Committee (IEC) of the Third Affiliated Hospital of Henan University of Traditional Chinese Medicine (approval number: 2025HL-017) before the study commences. In accordance with the Declaration of Helsinki and the requirements of the Good Practice for Clinical Research of Drugs, subjects will provide written informed consent after a full explanation of study aims, potential adverse events, and rights, including the right to withdraw from the study at any time without explanation.

## Discussion

The proposed study aims to evaluate the potential therapeutic effects of acupuncture and exercise (running and Tai Chi) on procrastination among college students and to elucidate the underlying cognitive mechanisms. Procrastination is a complex behavioral disorder involving multiple neural networks regulating self-control, emotion, and motivation by reward. The study design fully considers the multidimensional neural mechanisms of procrastination by measuring electrophysiological biomarkers reflecting cognitive control, attention sharing, and error detection ability (such as the ERPs P300 and N200) in addition to psychometric scale scores. It is anticipated that these multimodal measurements will provide a more comprehensive understanding of the neural mechanisms underlying procrastination, identify the most appropriate evidence-based interventions, and reveal potential biomarkers for future mechanistic and clinical investigation.

Acupuncture and exercise have numerous advantages as non-pharmacological interventions for neuromodulation and physiological regulation, respectively. Acupuncture may improve procrastination behavior by modulating brain self-control networks (including the dlPFC and ACC) and emotion regulation networks (involving the insula and OFC), while exercise may further enhance the effects of acupuncture-induced neuromodulation by promoting neuroplasticity and improving emotional regulation. The study design provides a comprehensive framework for exploring the efficacy of different interventions (acupuncture vs. running and Tai Chi) and a foundation for future studies testing combined interventions for the non-pharmaceutical treatment of procrastination.

This RCT will strictly follow the CONSORT and STRICTA guidelines to ensure scientific rigor. The sample size was set based on statistical principles, and is sufficient to compensate for participant attrition, which is expected to be low given that the interventions are non-invasive, safe, and scheduled for convenience. Further, the proposed measurements were selected based on extensive research describing the neurological control impairments contributing to procrastination. For instance, acupoint selection (Baihui, Sishencong, Zusanli, Neiguan) is based on traditional Chinese medicine theories and these targets are documented to regulate self-control and emotion. Further, the exercise interventions (running and Tai Chi) have been studied extensively for physiological and psychological effects, and intensity will be preciselycontrolled through heart rate monitoring. The effects of these interventions on procrastination will also be assessed using multiple psychometric scales (the GPS and PASS) and ERPs (e.g., P300 and N200) reflective of cognitive control and emotion regulation for comprehensive evaluation at behavioral and neurophysiological levels.

Nonetheless, there are potential limitations and challenges. First, study participants will be college students to reduce possible response heterogeneity due to age, general health, and education among other factors. However, applicability of the results to other populations will require additional study. Future studies should extend recruitment to people of different ages and occupations to verify the generalizability of the findings. Second, the planned follow-up period is relatively short as both data acquisition and analyses will be labor-intensive. However, it may still be possible to schedule later follow-up dates. Future studies could also set longer follow-up periods to assess the longevity of these interventions and factors associated with recurrence. In addition, the study will not examine the broad physiological and psychological impacts of acupuncture and exercise, and will only indirectly assess the changes in neural networks through ERP indicators. Future research combining functional magnetic resonance imaging (fMRI) and other techniques is warranted to further reveal the cellular and circuit-level effects of acupuncture and exercise on brain networks relevant to procrastination.

This study will comprehensively assess the therapeutic effects of acupuncture and exercise on the EEG characteristics and cognitive control mechanisms of college students with high procrastination levels by combining multiple psychometric instruments and task-dependent ERP measures. The research design is based on extensive literature reviews and is of sufficient scale to detect statistically significant and reproducible outcomes. Future studies can further validate this study by expanding the sample size, extending the follow-up time, and combining multiple neuroimaging techniques.
